**Fig. 1 fig0001:**
[figure not shown]
Study flowchart.

### Subject data collection

Informed consent was obtained from every subject enrolled in the study.

A pre-test evaluation was performed for all volunteers in the study for data collection in electronic forms, collecting the following data:-Demographic data: age, area of residence, social status, level of education.-Anthropometric data and previous medical history: height, weight, BMI, respiratory pattern, blood pressure, peripheral saturation, chronic medication, previous medical conditions (particularly neurologic, respiratory and cardiovascular conditions), smoking status.-IPAC-breve questionnaire was used to evaluate Physical Activity Index.

### Primary outcome measurements

Primary outcome is the increase in strength and lung function in the test groups compared to the sham group.

Lung function was performed with spirometry evaluation. Forced vital capacity (FVC), Forced Expiratory Volume in 1 S (FEV1), FEV1/FVC Ratio, Maximal Voluntary Ventilation (MVV) were the spirometry parameters evaluated using the SPM-A spirometer (CONTEC, China).

Inspiratory muscle endurance will be measured with Powerbreathe K5 equipment (Powerbreathe, Southam, England), using the S-INDEX, Flow and Volume. The handgrip strength will be checked using a hydraulic dynamometer (Saehan, Beijing, China).

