### Sample size and subject recruitment

The volunteers were recruited after posting invitation posters on the campus of the Federal University of Amazonas. No compensation was offered for participation in the experiment. All the subjects were female. The rationale for this was the ease of recruiting female participants, since there are activities taking place on the university campus only for elderly female.

Were inclusion criteria for the young group – ages comprehended between 18 and 25, no medical history of cardiovascular, pulmonary or neurologic conditions affecting the respiratory tract. Regarding the elderly group the inclusion criteria were the same, except the timeframe, considering ages between 60 and 80 years of age. Exclusion criteria were subjects out of the timeframe requested by the study protocol in both groups, medical history of cardiovascular, pulmonary or neurologic conditions. Also, in the selection of volunteers for the young group, those who were at the time of their menstrual period were excluded to avoid any hormonal influence on the results.

For the sample size, inspiratory muscle strength will be used through the dynamic inspiratory pressure (*S index*). As there is no study that evaluated this type of variable associated with tDCS, we will accept a priori a Cohen's size effect *F* = 0.25 (Small Effects). For sample size, ANOVA two-way repeated measures (Between-within) was calculated. Parameters used were size effect 0.25, α = 0.05, β = 80 %, 2 groups, 2 measurements (tDCS stimuli and Sham stimuli), correction between measurements = 0.5 and correction of no-sphericity ε = 1. Accepting a possible 20 % of sample loss, a sample calculation of 40 volunteers was selected both for the elderly and young group, with a global total of 80 subjects and G power 3.1 (University of Dusseldorf, Dusseldorf, Germany) was used for calculation.

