### Statistical analysis

The data will be expressed as mean and standard deviation of the mean, median and interquartiles, and percentage. Initially, normality will be tested using the Shapiro Wilk test and homogeneity using Levene's test. For mean analysis, the unpaired *t*-test or Mann-Whitney test will be used. For the evaluation of the intervention, ANOVA two-way (between-within) *post hoc* Bonferroni test will be used. If normal values are not present, the Kruskal-Walli's test will be performed for unpaired values and the Friedman test for paired data, with Bonferroni correction for the *p*-value. Effect size calculation will be done using the G*Power 3.1 software, and statistical analysis will be conducted using the JAMOVI software (Jamovi project, Australia) and GraphPad Prism 8.0 (GraphPad, USA). Significant values accepted as *p* < 0.05

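### Eight unranked measures share primary status at p < 0.05 with no stated adjustment across them, although the trial was sized on a single S-index test

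*Protocol article*

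**What the plan says.** The section Primary outcome measurements defines the outcome in one sentence: "Primary outcome is the increase in strength and lung function in the test groups compared to the sham group". The measures follow under the same heading:

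- Spirometry: "Forced vital capacity (FVC), Forced Expiratory Volume in 1 S (FEV1), FEV1/FVC Ratio, Maximal Voluntary Ventilation (MVV) were the spirometry parameters evaluated".
- Powerbreathe device: "Inspiratory muscle endurance will be measured with Powerbreathe K5 equipment (Powerbreathe, Southam, England), using the S-INDEX, Flow and Volume".
- Grip: "The handgrip strength will be checked using a hydraulic dynamometer".

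No measure is put first, no success rule is given, and the article names no secondary outcomes.

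The section Sample size and subject recruitment builds on one variable: "For the sample size, inspiratory muscle strength will be used through the dynamic inspiratory pressure", identified there as the S-index. It uses f = 0.25, alpha 0.05 and 80% power (printed as beta), and arrives at 40 per age group, 80 in all. It does not call the S-index the primary outcome.

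The section Statistical analysis gives the threshold, "Significant values accepted as *p* < 0.05". Bonferroni appears twice: with the parametric model ("ANOVA two-way (between-within) *post hoc* Bonferroni test will be used") and with the Kruskal-Wallis and Friedman fallback, where the family to be corrected is not defined.

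The step-by-step design has two stimulation sessions, cathodal on Day 2 and reversed polarity on Day 3, each with tests before and after. The Specifications table plans comparisons within each age group and between the two.

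**The concern.** A primary outcome has to tell the reader which test decides the trial. Here the primary section offers eight candidates, while the sample size section points to one that the primary section does not single out. Bonferroni on post hoc contrasts protects comparisons inside one ANOVA. It does nothing for the choice among eight ANOVAs, or among sessions and age groups.

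If a significant result on any measure may be reported as an increase in strength and lung function, the 5% error rate used for sizing does not apply to the main claim. The Protocol validation section says data analysis is under way, so an unranked list also leaves room to settle on a lead measure after results are visible.

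There is a labelling conflict as well. The S-index stands for inspiratory strength in the sample size section and is listed as a measure of inspiratory endurance in the primary outcome section.

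**Working it through.** **1. Reproduce the planned size.** Inputs from Sample size and subject recruitment: f = 0.25, alpha = 0.05, power 80%, 2 groups, m = 2 measurements, correlation 0.5, epsilon 1. Taking the within-between interaction, the noncentrality is λ = N·f²·m/(1 − ρ), with 1 and N − 2 degrees of freedom.

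- N = 34: λ = 34 × 0.0625 × 2/0.5 = 8.5, power 80.7%. N = 33 gives 79.5%. So 34 per age group is the smallest even number that reaches 80%.
- With 20% added: 34 × 1.2 = 40.8, close to the stated 40.

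The plan's figure is therefore the size for **one** test at 0.05 in each age group.

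**2. Count the primary measures.** Spirometry 4 + Powerbreathe 3 + handgrip 1 = 8. In the day-by-day description, the FVC and FEV1 manoeuvre is set out on Day 1, and Day 2 spirometry spells out only MVV. The measures clearly repeated before and after stimulation are MVV, S-index, Flow, Volume and handgrip, which makes 5.

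**3. Chance of at least one false positive, independent tests.** The formula is 1 − (1 − a)^k, with a = 0.05 for either direction and a = 0.025 for the benefit direction only.

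| Tests k | What is counted | Either direction | Benefit only |
|---|---|---|---|
| 5 | repeated measures, one session, one age group | 22.6% | 11.9% |
| 8 | all listed, one session, one age group | 33.7% | 18.3% |
| 10 | 5 measures × 2 age groups | 40.1% | 22.4% |
| 32 | 8 measures × 2 sessions × 2 age groups | 80.6% | 55.5% |

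**4. Allow for correlation.** The article gives no correlation between outcomes, so these values are assumptions. They come from simulation with equal correlation r among the outcomes.

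- 8 tests, either direction: about 25% at r = 0.5 and 19% at r = 0.7. Benefit only: about 12% and 10%.
- 5 tests, either direction: about 18% and 15%. Benefit only: about 9% and 7%.
- 32 tests, either direction: about 60–69% at r = 0.5 and 47–57% at r = 0.7, depending on the correlation assumed between sessions. Benefit only: about 34–41% and 25–33%.

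The reference rate is 5% in either direction and 2.5% for benefit.

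**5. What control would cost.**

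- One S-index test in each of two age groups at 0.05: 1 − 0.95² = 9.75%.
- The same two tests at 0.025: 1 − 0.975² = 4.9%. Power at f = 0.25 is about 71% with N = 34 and 79% with N = 40 per age group.
- Keeping all eight as primary at 0.05/8 = 0.00625 in one age group: power about 50% with N = 34 and 61% with N = 40.

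**The case against.** Several points can fairly be put against this, and some of them limit what may be claimed.

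- **A chance positive is more likely than not.** A reader might infer this, but the documents do not support it. It needs something like 32 separate two-sided tests, and the article never says that each session and age group is tested separately. Even then it depends on the assumed correlation (47–57% at 0.7). The outcome is worded as an increase, and in the benefit direction the 32-test figure is below one half once correlation is moderate.
- **Any one result is enough.** No such rule is written. Strength and lung function could be read as requiring both. The percentages above are conditional on the any-one reading, which the text neither adopts nor excludes.
- **The stated power belongs to the S-index only.** This goes too far. The effect size of 0.25 is generic, chosen because no earlier data existed, so the same power holds for any measure with that standardised effect and correlation. What remains is that the size was calculated for one test.
- **Strength or endurance.** That one result would be used for both claims is speculation. The inconsistent label is in the text.
- **Exploratory trial, analysis plan not shown.** The abstract presents the study as a bridge to larger ones, and multiplicity detail often sits in an analysis plan. The Bonferroni correction for the rank tests has no defined family, so it cannot be ruled out that a wider one was meant. But the article does fix a primary outcome and a threshold, and its primary outcome and sample size sections do not agree on which variable the trial is built around. That is a defect in what is stated, not an omission.

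**Conclusion.** The point holds in a limited form. Eight measures have equal primary status, the threshold is 0.05, and no adjustment is stated across outcomes, sessions or age groups, while the trial was sized for a single S-index test. Followed as written, the plan does not hold the primary claim at 5%.

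If any one result can carry the claim, the either-direction risk within one session and one age group is about 34% for eight independent tests and about 25% at an assumed correlation of 0.5. For the five clearly repeated measures it is about 23% if independent. Every figure falls with correlation or when only benefit counts, but all the scenarios calculated stay well above the nominal rate. The 81% for 32 independent tests is an upper bound on an inferred count and should not be quoted as the trial's error rate.

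**What to change.** 1. Name one primary outcome: the S-index pre-to-post change, active versus sham, in the Day 2 cathodal session. It is the variable used for sizing, and cathodal stimulation is what the research questions ask about.
2. State how error is controlled over the two age groups. Either use one age-stratified arm contrast at 0.05 with age-by-arm as secondary, or test at 0.025 in each age group. Restate the power in either case; for the second option it is about 71% with N = 34 and 79% with N = 40 per age group.
3. Make the other seven measures and the Day 3 session secondary with Holm adjustment, or label them exploratory.
4. Use one label for the S-index throughout, reconciling strength in the sample size section with endurance in the primary outcome section.
5. Because analysis is already under way, record the choice before arm-level results are seen. If they have been seen, report it as post hoc.

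The change takes about a paragraph and needs no new data. The price is that spirometry, Flow, Volume, handgrip and Day 3 results can no longer carry the primary claim, and that power is somewhat lower if alpha is split by age group.

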### tDCS placement and technical aspects

For the intervention with the tDCS we used the neuromodulator from Microestim Foco Research, (NKL, Santa Catarina, Brazil). For every subject two devices were used to achieve bilateral stimulation. The cathode was placed in the C3 and C4 motor regions by 10/20 EEG bilaterally and the anode over the supraorbital region, also bilaterally – Fig. 2. All experiments were conducted with a 2 mA current for 30-minute period. The sham group will be subjected to the same protocol placement applied for intervention group; however, those volunteers will not receive any electrical stimulation, according to sham program from the device

**Fig. 2 fig0002:**
[figure not shown]
tDCS placement, A) cathodic stimulation; B) anodic stimulation. Both young and elderly group with a 30-minute 2 mA stimulation versus no stimulation.

The technician performing the intervention had previous experience in the use of tDCS in research and healthcare dataset.

### Step-by-step study design

The study is designed as an experimental and double blind randomized, summarized in Fig. 1.

### Day 1

All volunteers were evaluated initially for the presence of any exclusion criteria. After, a social demographic and anthropometric evaluation was conducted. Also, the patient's relevant medical history was recorded.

All subjects underwent baseline spirometry under controlled environmental conditions. The patient was seated and instructed to perform normal ventilations for 5 s, after a therapist command a slow expiration, followed by inspiration and forced expiration. For all participants, the device estimated a value of FVC and FEV_1_ by predicted values. A minimum of 3 and a maximum of 8 maneuvers were performed. At least 3 of these maneuvers would have to be acceptable and reproducible. Thus, differences greater than 10 % in the highest values of CVF or FEV_1_ were not admitted. The highest value of the series was chosen for both parameters in the study. The test would be stopped or restarted in the event of adverse effects such as cough or lipothymia.

### Day 2

All subjects were evaluated, within 24 h from day 1 evaluation, prior to any intervention, in quiet and temperature regulated conditions, with:-Handgrip strength. The volunteers were seated with their feet well supported, with the elbow at 90° stabilized by the evaluator at the time of the measurement. The test was performed for 3 s, followed by a 1-minute break, with repetition of the intervention for two more rounds. The highest values of the 3 rounds were picked for the study.-Spirometry evaluation with evaluation of the MVV. The patient was seated and was instructed to inhale and exhale quickly and deeply for 12 s. Up to 5 measurements were taken, choosing the one with the highest peak, as long as the variation was not greater than 10 %.-Evaluation of dynamic inspiratory strength with Powerbreathe (Powerbreathe, Southam, England). With the subject seated and using a nose clip, the patient is instructed to inhale quickly and deeply through the mouthpiece with slow exhalation to the limit achieved. Followed by pause and repetition of the movement, The volunteers performed a warm-up of 5 inhalations before the assessment, which went up to a maximum of ten repetitions (Silva et al., 2018). The chosen value would be the maximum among the repetitions.

#### Intervention with tDCS

-The tDCS was performed in the test group with a 2 mA current for a 30-minute period, with the electrodes positioned has previously explained.-During the intervention the patient was asked to remain quiet and still. The evaluator actively asked for the presence of any side-effect.

#### Post – intervention evaluation

-After the intervention with tDCS the patients repeated all the tests performed prior to intervention in the same technical and environmental conditions.

### Day 3

The evaluation in day 2 was conducted 48 to 72 h after the day 2 assessment. The environmental conditions were similar.

The pre and post intervention test were the same and conducted as described.

Regarding the intervention with tDCS the electrodes switched position with the anode being placed at C3 and C4 motor regions bilaterally and the cathode over the supraorbital region, also bilaterally. The intervention was then performed with the same parameters described for day 2 evaluation.

### Statistical analysis

The data will be expressed as mean and standard deviation of the mean, median and interquartiles, and percentage. Initially, normality will be tested using the Shapiro Wilk test and homogeneity using Levene's test. For mean analysis, the unpaired *t*-test or Mann-Whitney test will be used. For the evaluation of the intervention, ANOVA two-way (between-within) *post hoc* Bonferroni test will be used. If normal values are not present, the Kruskal-Walli's test will be performed for unpaired values and the Friedman test for paired data, with Bonferroni correction for the *p*-value. Effect size calculation will be done using the G*Power 3.1 software, and statistical analysis will be conducted using the JAMOVI software (Jamovi project, Australia) and GraphPad Prism 8.0 (GraphPad, USA). Significant values accepted as *p* < 0.05

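### A Shapiro-Wilk result on outcome values decides whether an outcome gets the powered between-within ANOVA or rank tests that do not address arm-by-time

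*Protocol article*

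**What the plan says.** The Statistical analysis section of the protocol article sets a sequence. First comes the check: "Initially, normality will be tested using the Shapiro Wilk test and homogeneity using Levene's test". The planned analysis of treatment is then named: "For the evaluation of the intervention, ANOVA two-way (between-within"), with Bonferroni post hoc tests. Then comes the switch: "If normal values are not present, the Kruskal-Walli's test will be performed for unpaired values and the Friedman test for paired data". Group comparisons have a similar alternative, with no criterion of their own: "For mean analysis, the unpaired *t*-test or Mann-Whitney test will be used". The overall threshold is "Significant values accepted as *p* < 0.05".

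The condition is worded for values; residuals and changes are not mentioned. Levene's test is listed, but no consequence of its result is stated. The level of the pre-test is not given, nor whether it is applied per cell, to pooled values or to residuals.

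Sample size and subject recruitment bases the sample size on the S-index and on the two-way between-within ANOVA.

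**The concern.** The stated trigger tests the wrong quantity. With one pre and one post measurement, the arm-by-time test in a between-within ANOVA is the active-versus-sham comparison of within-subject change. A stable, skewed spread between women in S-index or FVC cancels out of the change, yet it can fail a normality test on the values.

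The consequence of a switch is not neutral either. Kruskal-Wallis on unpaired values and Friedman on paired values are not tests of arm-by-time. A chance rejection therefore changes the question being answered, and different outcomes in the same report can end up answering different questions. For the S-index, the test reported might not be the one the trial was powered for.

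**Working it through.** **Inputs from the protocol**
- Sample size and subject recruitment: "Parameters used were size effect 0.25, α = 0.05, β = 80 %, 2 groups, 2 measurements (tDCS stimuli and Sham stimuli"), and "correction between measurements = 0.5 and correction of no-sphericity ε = 1". The 80% is read as power. The study steps measure before and after stimulation, so the two measurements are taken as pre and post.
- The same section plans 20 per randomised group. The specifications table gives 68 in total, which is 17 per group.
- Primary outcome measurements lists eight measures: FVC, FEV1, FEV1/FVC, MVV, S-index, Flow, Volume and handgrip.

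**Assumed, because not stated:** a pre-test level of 5%, the unit tested, all outcome distributions, and how the fallback tests would be applied.

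**Step 1: the plan's own figure.** For the within-between interaction, λ = f²·N·m·ε/(1−ρ) = 0.0625 × 34 × 2 × 1 / 0.5 = 8.5. A noncentral F with 1 and 32 degrees of freedom gives power 0.807, and N = 34 is the smallest even total reaching 80%. Two age groups give 68, the figure in the specifications table. (The within-subject main effect gives the same N; the between-arm main effect would need 98.) The stated size therefore fits the interaction test.

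**Step 2: what that test depends on.** With two times, the interaction F is the square of the two-sample t on d = post − pre. Subject level drops out of d, so the relevant normality is that of d within arm.

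**Step 3: how often exactly normal data would be switched.** For c independent tests, P(at least one rejection) = 1 − 0.95^c. The simulations used 20,000 data sets with correlation 0.5.
- One test on residuals: 5% by formula; 4.9-5.0% simulated.
- Four cells (2 arms × 2 times, one age group): 1 − 0.95⁴ = 18.5%; simulated 18.1% at 20 per cell and 18.5% at 17.
- Eight cells (both age groups): 1 − 0.95⁸ = 33.7%; simulated 33.3-33.5%.

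At about 18% each, 8 × 0.18 ≈ 1.4 of the eight measures would be switched on average.

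**Step 4: skewed levels with normal changes.** This is one illustrative case, assuming log-SD 0.3, mean 70 and error SD 7. Testing four raw cells triggers the switch in 47-49% of trials at 20 per arm and 42% at 17. Testing the changes in each arm triggers it in about 10%. The fair benchmark for four tests is the 18.5% of step 3, because the 10% comes from only two tests (1 − 0.95² = 9.8%). The ANOVA's normality assumption holds in all these data sets.

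**Step 5: what a switch costs.**

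*Same contrast kept* (t-test, or Kruskal-Wallis on the change after a switch; 20 per arm, four-cell trigger, 10,000 trials per scenario). Two-stage type I error is 5.2% (ρ = 0.5), 4.8% (ρ = 0.8) and 4.8% (the skewed case). Power is 85.5%, 86.8% and 85.4%, against 85.9%, 87.2% and 86.2% for the fixed test.

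*Friedman read within the active arm*, with a 0.5 SD practice gain in both arms and no treatment effect. With two times, Friedman is a sign test. With 20 women, (2k−20)²/20 > 3.84 requires k ≥ 15 or k ≤ 5.
- ρ = 0.5: SD of change = √(2 × 0.5) = 1; P(rise) = Φ(0.5) = 0.69; significant in 38%. Two-stage: 0.82 × 0.05 + 0.18 × 0.38 = 11%.
- ρ = 0.8: SD of change = √(2 × 0.2) = 0.63; P(rise) = Φ(0.79) = 0.785; significant in about 75%. Two-stage: 0.82 × 0.05 + 0.18 × 0.75 = 18%.

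The fixed interaction test stays at 5% in both.

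*Kruskal-Wallis on post values*, ρ = 0.8, with an assumed difference in change of 0.6 raw SD. Power falls from 83% to 45% for an outcome that is switched. Averaged over all trials, it is 0.82 × 0.83 + 0.18 × 0.45 = 76%. At ρ = 0.5 and a 1 SD difference, little is lost (85% against 86%).

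**The case against.** The strongest reply is that checking normality first is common practice and that the trigger by itself does almost nothing. Step 5 bears this out: if the fallback still compares changes between arms, type I error stays near 5% and the power loss is under one percentage point. That stands, and it limits the point. It does not clear the plan as written, because the plan's fallbacks are described only as tests for unpaired and for paired values, and neither is an arm-by-time test.

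A condensed article may also leave the unit of a diagnostic test to a fuller plan. That is accepted, which is why a range is given and not one rate.

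A reader might infer three stronger claims that the document does not support:
- That Levene's test also selects the analysis. It is listed, but only non-normality leads to a different test.
- That about half of normal outcomes would be switched. That takes 16 cells (arm × age × session × time), which does not fit the stated two-way model. Days 2 and 3 also use reversed electrode positions.
- That pre-testing as such invalidates the 0.05 threshold. The calculation with the contrast kept shows otherwise.

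**Conclusion.** The point holds in a limited form. A normality test on values, not on changes or residuals, decides whether an outcome receives the powered between-within ANOVA. Switching of exactly normal data ranges from 5% to about one third, depending on an unstated unit and an assumed 5% level. The 42-49% in the skewed case is one assumed illustration, since the protocol gives no outcome distributions.

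The damage comes mainly from what the switch leads to. False positives of 11-18% and the power of 45% for a switched outcome both depend on how the fallbacks are applied (Friedman within the active arm, Kruskal-Wallis on post values) and on the assumed practice gain, effect and correlation. Little is gained in return: with equal planned arms of 20, a comparison of mean changes tolerates moderate non-normality. The rule should be changed, but the randomised comparison itself is not compromised.

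**What to change.** In Statistical analysis, delete the rule that a normality result selects the test. State that every outcome is analysed with the same prespecified between-within model, equivalently the active-versus-sham comparison of within-session change. Check residuals graphically. Shapiro-Wilk and Levene results may be reported as description, with no analysis choice tied to them. Report a permutation (re-randomisation) or bootstrap p-value for the same contrast as a fixed sensitivity analysis, whatever the residuals look like.

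The cost is a few sentences and slightly more analysis work, with no new data. Protocol validation describes the analysis as ongoing, so the change must be dated and disclosed as made at that stage.

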**Table utbl0001:** 

Subject area:	Neuroscience
More specific subject area:	Effects of bilateral cathodal tDCS application in muscle strength and pulmonary performance in the young and elderly population.
Name of your protocol:	Bilateral transcranial direct-current stimulation on muscle strength and respiratory endurance: randomized, placebo-controlled, double-blind trial protocol
Reagents/tools:	Bilateral tDCS: Neuromodulator from Microestim Foco Research, NKL, Santa Catarina, Brazil. Forced vital capacity (FVC), Forced Expiratory Volume in 1 S (FEV1), FEV1/FVC Ratio, Maximal Voluntary Ventilation (MVV): SPM-A spirometer CONTEC™, China Powerbreathe K5 equipment (Powerbreathe, Southam, England): S-INDEX, Flow and Volume. Handgrip strength: hydraulic dynamometer (Saehan, Beijing, China).
Experimental design:	Randomized placebo-controlled double-blind trial. Four groups (*n* = 68), test (young and elderly, *n* = 34) and placebo (young and elderly, *n* = 34). Outcome measures were evaluation of lung function, strength of inspiratory muscles, general strength. After a basal evaluation, the outcomes were tested in two separated moments before and after bilateral cathodal tDCS stimulation both comparing in the same age group and comparing elderly versus young.
Trial registration:	U1111–1310–2605, International Clinical Trial Registry Platform
Ethics:	The study was conducted in line with recommendations from the Declaration of Helsinki and received ethical approval from the Ethics Committee of the Federal University of the Amazonas, Brazil [CAAE66350622.0.0000.520, evaluation 315.763].
Value of the Protocol:	tDCS is proven to be a valuable tool in rehabilitation and performance enhancement in several areas, but with little or no work done in respiratory function or respiratory rehabilitation. The main objective is to evaluate the expected improvement of the respiratory muscle strength and resistance after intervention with bilateral tDCS over the primary motor cortex in healthy young and elderly subjects. It is a randomized, double-blinded study designed to study the possibility of using tDCS for enhance respiratory performance in healthy subjects or in rehabilitation programs after respiratory injury. We highlight the construction of the study, allowing the comparison between the response in the young and the elderly.

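### The stated target is the gain over sham, but the sizing text mislabels it and the analysis rule does not make the arm-by-time contrast decisive

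*Protocol article*

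**What the plan says.** All places are in the protocol article.

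- **Primary outcome measurements:** "Primary outcome is the increase in strength and lung function in the test groups compared to the sham group". This is a between-arm difference in pre-to-post change. The first item under Research questions also compares with controls.
- **Sample size and subject recruitment:** the design sized is described by "ANOVA two-way repeated measures (Between-within) was calculated", with "2 measurements (tDCS stimuli and Sham stimuli), correction between measurements = 0.5". The text that follows, on randomization, assigns each participant to tDCS or placebo, 20 per arm in each age group. No participant is described as receiving both.
- **Specifications table, Experimental design:** after listing test and placebo groups, it says "the outcomes were tested in two separated moments before and after bilateral cathodal tDCS stimulation both comparing in the same age group and comparing elderly" with young subjects.
- **Statistical analysis:** "For the evaluation of the intervention, ANOVA two-way (between-within) *post hoc* Bonferroni test will be used". If normality fails, Kruskal-Wallis is used for unpaired and Friedman for paired data, with Bonferroni correction. The threshold is given as "Significant values accepted as" p < 0.05. The factors, the deciding term and the post hoc pairs are not named.
- **Protocol validation:** repeats the model name and says that data analysis is ongoing.

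**The concern.** Within one outcome, session and age group, a 2 × 2 between-within ANOVA gives three F tests: arm, time, and arm by time. Only arm by time corresponds to the stated primary outcome. The time effect is non-zero whenever both arms improve on repetition. The arm effect averages pre and post values, which dilutes a real effect. Bonferroni post hoc tests, as usually run, compare cell means: pre with post within an arm, or active with sham at one time. None of these is a difference between arms in change. With two paired measurements, a Friedman test is likewise a within-group before-after test.

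The outcomes are maximal-effort manoeuvres (handgrip, MVV, dynamic inspiratory strength) repeated after stimulation in the same visit. A practice or warm-up change shared by both arms is plausible, and removing it is the purpose of the sham arm. A conclusion drawn from significance in the active arm and none in sham would not use that control properly. Reading the arm main effect could miss a true effect.

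**Working it through.** **1. The plan's own figure.** The inputs come from Sample size and subject recruitment: "Parameters used were size effect 0.25", α = 0.05, power 80% (written as β = 80%), k = 2 groups, m = 2 measurements, correlation ρ = 0.5, ε = 1.

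For the interaction or the within-subject main effect, λ = f²·N·m/(1 − ρ), with 1 and N − 2 df.

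- N = 34: λ = 0.0625 × 34 × 2 / 0.5 = 8.5, power 0.807. This is the smallest even N that reaches 80%.
- N = 40: λ = 10, power 0.869.
- 34 × 1.2 = 40.8, close to the stated 40 per age group. Two age groups of 34 give the 68 in the Specifications table.

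For the between-arm main effect, λ = f²·N·m/(1 + ρ).

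- N = 40: λ = 0.0625 × 40 × 2 / 1.5 = 3.33, power 0.43. It would take N = 98 to reach 80%.

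The stated size therefore fits the arm-by-time term, but it fits the within-subject main effect equally well. It does not show which was meant.

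**2. What f = 0.25 means for the interaction.** With ρ = 0.5, the SD of change equals the SD of the outcome, since √(2 × (1 − 0.5)) = 1. Cell deviations of ±0.25 SD give a difference in change of 4 × 0.25 = 1.0 SD. Check: with 17 per arm, 1.0/√(2/17) = 2.915, and 2.915² = 8.5, the λ above.

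**3. What happens if within-arm tests decide.** Simulation with 100,000 trials per row, 20 per arm, ρ = 0.5, no tDCS effect, and the same gain in both arms. Within-arm tests use the pooled error and Bonferroni over 2 or 6 comparisons. The shared gain is an assumption, because the document gives no figure for it.

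| Shared gain (SD of change) | Active improved, sham did not: 2 tests | Same, 6 tests | Arm by time significant |
|---|---|---|---|
| 0 | 1.3% | 0.5% | 5.1% |
| 0.2 | 7.5% | 3.6% | 4.9% |
| 0.3 | 13.8% | 7.7% | 5.0% |
| 0.5 | 23.8% | 20.3% | 5.0% |
| 0.8 | 9.6% | 16.3% | 5.0% |

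The discordant pattern falls again at 0.8 SD because sham then also tends to be significant. The active-arm test taken alone keeps rising: with 2 tests it is significant in 17%, 47% and 89% of trials at gains of 0.3, 0.5 and 0.8 SD.

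Hand check at 0.5 SD. Each within-arm test is significant in 46.6% of trials, and if the two were independent the discordant rate would be 0.466 × 0.534 = 24.9%. The simulated 23.8% is slightly lower because the tests share an error term. The time main effect has noncentrality 0.5 × √40 = 3.16 and is significant in about 87% of trials.

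**4. The non-normal branch.** Kruskal-Wallis on unpaired values and Friedman on paired values each address one margin of the design. Neither tests whether change differs between arms unless it is applied to change scores, and the text does not say that it is.

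**The case against.** A reader might infer that the plan never fixes a sham comparison and offers three rival ones. The document does not support that. The primary outcome and the first research question both state the comparison with controls. The Specifications table names placebo groups immediately before the sentence quoted, and comparing within the same age group can readily mean test against placebo. The between-within ANOVA does produce the needed interaction test. Factor labels and lists of post hoc pairs are often left to a fuller document.

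The mechanism is also partly inferred. The post hoc pairs are not listed, and post hoc tests usually follow an overall test. If they were read only after a significant interaction, the discordant pattern would occur in at most 2.4% of trials for shared gains up to 0.75 SD. The size of the gain is not documented either. Taking the best of repeated manoeuvres, and the five warm-up inhalations before the inspiratory test, may reduce it.

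Three things still stand. The description of tDCS and sham as repeated measurements contradicts the parallel allocation. The analysis rule neither names the interaction nor makes post hoc tests conditional on it. The non-normal branch, as written, drops the interaction altogether.

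**Conclusion.** The point holds in limited form. The target is stated correctly, but the sizing and analysis text do not carry it through, and on the non-normal branch it is not tested as written. If within-arm results are read as efficacy, the discordant pattern arises by chance in about 20–24% of null trials. This rests on 20 per arm, ρ = 0.5, an assumed shared gain of 0.5 SD of change and Bonferroni tests read unconditionally. With no shared gain the rate is about 1% or less. Arm by time stays at about 5% whatever the gain.

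It would go too far to say that the sham control is lost, or that the plan's false-positive rate is 20–24%: the text permits that reading but does not require it. The correction should be made, because it is cheap and it settles what counts as evidence that tDCS works.

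**What to change.** - **Statistical analysis.** State that, for each outcome and session within each age group, the effect of tDCS is judged by the active-versus-sham difference in pre-to-post change (arm by time), with a 95% CI. When data are non-normal, use a between-arm comparison of change scores, for example the Mann-Whitney test that the section already names. Main effects, within-arm tests and cell-mean post hoc tests are descriptive.
- **Specifications table, Experimental design.** State the comparison as active versus sham change within each age group. Keep elderly versus young, the second research question, as the difference between age groups in that active-versus-sham effect.
- **Sample size and subject recruitment.** Label the two measurements as before and after stimulation, and the two groups as tDCS and sham.

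The cost is wording in three places. No new data are needed, and N = 34 per age group is unchanged for the comparison within an age group. Because Protocol validation says analysis is ongoing, the change must be dated and disclosed as made at that stage. The small downside is that a before-after gain in the active arm alone can no longer be reported as efficacy.
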